## **3. INTERVENTION**

### **3.1 INTERVENTION OVERVIEW**

ZINC is a double-blinded randomized control trial to assess the efficacy of zinc supplementation vs. placebo among HIV-positive Russians, who are ART-naïve at enrollment with a recent history of heavy drinking. Participants will be randomly assigned to receive either zinc supplementation or placebo to be taken orally daily over 18 months.

### **3.2 RANDOMIZATION**

ZINC randomization will be assigned in a 1:1 ratio to zinc or placebo utilizing block randomization where stratification will be based upon gender and heavy alcohol consumption during the past week to ensure balance. The randomization, stratification and assignment of participants to the two treatment groups will be conducted and monitored by the URBAN ARCH Biostatistics and Data Management (BDM) core. The software package SAS will be used to generate randomization lists to assign participants as they are enrolled into the clinical trial. The study pharmacist will receive the list of randomization IDs with group assignment and will provide packaged boxes of study medication to the study team.

Following completion of the baseline assessment, the RA will be directed to the electronic randomization screen, which will provide a checklist of all components that need to be completed prior to randomization. Randomization will not be able to proceed until all outstanding questions are resolved (e.g., contact information and 7-day alcohol use entered into the electronic system). Once submitted, the randomization page will automatically assign the participant to a randomization ID. The RA will then retrieve the box of study medication labeled with the correct randomization ID and label the box with the participant study ID, thus linking the two numbers. As a double-blinded study, ZINC participants, investigators, RAs and the study nurse will be unaware of participant group assignment.

### **3.3 INTERVENTION**

Participants randomly assigned to the intervention (zinc) group will receive study medication at all but the final visit. Of the eight study visits, four include longer assessments with lab work and four are shorter medication adherence checks.

Zinc capsules will be compounded using pharmacy-grade zinc gluconate and Riboflavin (adherence measure) at Bios Pharmaceuticals in St. Petersburg. Zinc capsules for men and women will contain 15 and 12 mg of zinc gluconate, respectively, as this dose had been shown to be effective in previous trials and has minimal risk of adverse events. The capsules will be provided in bottles, each containing a 28-day supply of medication, labeled differently for males and females.

Participants will be instructed to take one pill daily by mouth with a full glass of water, at the same time they take any other medications. If participants are not taking any other medications, they will be told to take the study drug at the same time each day. Participants will be instructed to not eat food or drink beverages containing caffeine 1-2 hours before or after taking the medication and to never take more than one pill per day. The latter is due to its potential interaction with zinc absorption.

Individuals using zinc supplements could experience adverse effects if they take more zinc than provided. These adverse effects could include nausea, vomiting, diarrhea, and abdominal pain. Normally, these adverse effects are seen in people who regularly consume at least 40mg-1000mg/day. In order to help prevent these adverse effects, participants will be instructed not to take more zinc supplements than what was provided by the study. Study research staff will also monitor participants for signs of zinc overdose. These adverse effects are not expected to be likely.

Zinc may decrease the body's absorption of two kinds of antibiotics, quinolones and tetracyclines, which include: Ciprofloxacin (Cipro), Levofloxacin (Levaquin), Ofloxacin (Floxin), Moxifloxacin (Avelox), Norfloxacin (Noroxin), Gatifloxacin (Tequin), Tetracycline, Minocycline (Minocin), Demeclocycline (Declomycin), Cinoxacin (Cinobac), Enoxacin (Penetrex), Gemifloxacin (Factive), Grepafloxacin (Raxar), Sparfloxacin (Zagam). Participants will be advised to discontinue taking study medications while they are on antibiotics and to consult a physician for further guidance and information.

In accordance with FDA guidelines, the study did not require an Investigational New Drug (IND) application, as it was conducted outside of the United States.

### 3.3.A CONTROL

Participants randomized to the control group will receive all study procedures and instructions identical to the intervention group. Participants will receive a sucrose placebo identical to the zinc medication in appearance and taste. Riboflavin will be added to both active and placebo medication as a biologic adherence measure. Sucrose, for the placebo and Riboflavin, for the biologic adherence measure, will be obtained from the same pharmacy as the study medication for the intervention group.

## 3.4 MEDICATION CONSIDERATIONS

### 3.4.A SYMPTOM MONITORING

To minimize medication risks, participants will be monitored for adverse effects at each study visit. Participant symptoms will be assessed at baseline and any chronic conditions or symptoms that existed prior to introduction of study medication will be documented using an electronic Baseline Event form. During each subsequent study visit, the RA will ask the participant how they feel and review the list of symptoms of concern, beginning with any symptoms recorded at the previous visit and including the four

most frequent side effects of zinc: abdominal pain, diarrhea, nausea, and vomiting. The RA will ask about any new symptoms experienced by the participant since the last study visit. Any event that meets the criteria for an adverse event (AE), serious adverse event (SAE), or unanticipated problem will be recorded using paper and electronic AE and/or SAE forms. The site will receive the results of all blood work performed on study participants. Any abnormal lab results that are deemed clinically significant by the clinical team will be recorded as an AE and/or SAE and the participant will be referred to their local medical provider. All baseline events, AE and SAE forms will be reviewed by the US and Russian teams. All events will be presented to and reviewed by the Data and Safety Monitoring Board (DSMB).

Participants will also be alerted of possible interactions between zinc and certain antibiotics and instructed to discontinue the study drug and contact the study team should they initiate a course of antibiotic medication.

Participants will be encouraged to contact study personnel or another health care provider if they experience any adverse effects. Furthermore, every two months a report will be generated of participants who report taking more than one pill per day, or for those whose pill count adherence was greater than 100% at their previous study visit. The report will be reviewed by the US Project Manager and the Russian study team. Any questions or concerns will be brought forth to the study PIs.

#### 3.4.B. ADHERENCE

Medication adherence will be assessed at each study visit using direct (Riboflavin) and indirect (pill counts and self-report) measures.

##### **Direct Adherence Measures**

Riboflavin (50 mg), a vitamin yielding a change in urine color, will be added to both active and placebo capsules. Participants will be informed that the color change is harmless. At this dose, Riboflavin is expected to remain in the system at detectable levels for up to 24 hours. At each study visit post-baseline (while taking study medication), participants will be asked to provide a urine sample, which will be visually inspected for the presence or absence of Riboflavin in a room with low ambient light, using ultraviolet (UV) light at the long wave setting (33 nm).

##### **Indirect Adherence Measures**

###### *Pill Counts*

Participants will be instructed to bring any unused medication to each study visit post-baseline. The RA will count and record the number of remaining pills.

###### *Self-Report*

Medication adherence will also be measured through self-report using the modified Adult AIDS Clinical Trial Group (AACTG) ART adherence questions. At each post-baseline study visit participants will be

asked to draw a line on a paper ruler, numbered from 0-100, to indicate the number best representative of how much of the study medication they have taken in the past 6 weeks. Participants will also be asked questions about the longest period of time in which they consistently took the study medication, if they stopped taking the medication, and if they took more than one pill of study medication on any day in the past 6 weeks.

### **Adherence Aids**

During each study visit (for the exception of the 18-month visit) medication instructions will be reviewed and strategies for adherence will be discussed with each participant. Adherence plans will be individually tailored to each participant, depending on their reason for non-adherence. To further increase medication adherence, an automated text message will be sent twice per week for the first 6 weeks, reminding participants to take their study medication. At the 6-week appointment, the assessor will ask the participant whether the text messages are helpful and whether to continue, increase or decrease the frequency of the reminders. Participants will be able to reduce the frequency or opt out of text message reminders entirely at any time throughout the study.

#### **3.4.C. MEDICATION DISBURSEMENT**

Medication inserts will be provided to participants at baseline.

Participants will receive an extra 6-week of supply of study medication to accommodate instances of lost medication or missed visits. At subsequent study visits, the participant will be asked to bring in any unused medications. The assessor will count the number of remaining pills and redistribute them to the participant.

The pharmacist will deliver, at one time, six months-worth of study medications to the assessors at Pavlov State Medical University.

#### **3.4.D. LOST OR STOLEN STUDY MEDICATION**

If participants report lost or stolen medication, they will be provided with extra study medication. In the event that a participant reports losing medication more than once, the study team will be alerted and the case discussed to determine a plan of action.

#### **3.4.E. DISCONTINUATION OF STUDY MEDICATION**

Those who discontinue medication will be followed and analyzed by intention to treat.

Participants found to be pregnant during the study will have their study medication discontinued, but will still be followed-up for the duration of the study. Participants who report pregnancy outside of study visits will be instructed to immediately discontinue their study medication and asked to come in for a confirmatory urine pregnancy test.

## 3.5 SCHEDULE OF DATA COLLECTION

### 3.5.A. VISIT WINDOWS

#### 1. Screener B/Baseline Visit:

Window open: Date screened (A)

Window close: 30 days after being screened (A)

Window length: 30 days

*Following 30 days, screeners A and B (see 4.2 Screening) will be administered again if individual is interested in participating.*

#### 2. 6 Week Visit

Window open: 5 weeks post baseline

Window close: 9 weeks post baseline

Window length: 4 weeks (1 month)

#### 3. 12 Week Visit (3 months)

Window open: 9 weeks post baseline

Window close: 16 weeks (4 months) post baseline

Window length: 7 weeks

#### 4. 6 Month Visit

Window open: 4 months post baseline

Window close: 8 months post baseline

Window length: 4 months

#### 5. 9 Month Visit

Window open: 8 months post baseline

Window close: 11 months post baseline

Window length: 3 months

## 6. 12 Month Visit

Window open: 11 months post baseline

Window close: 14 months post baseline

Window length: 3 months

## 7. 15 Month Visit

Window open: 14 months post baseline

Window close: 17 months post baseline

Window length: 3 months

## 8. 18 Month Follow Up

Window open: 17 months post baseline

Window close: 21 months post baseline

Window length: 4 months

## 3.6 DATA SOURCES

### 3.6.A QUESTIONNAIRES

Participants will be assessed at baseline, 6-, 12- and 18-months post enrollment, along with shorter medication visits at 6-weeks, 12-weeks, 9-months and 15-months. All study assessments will take place at First St. Petersburg Pavlov State Medical University. On occasions when a study participant is unable to come to the study site for a face-to-face interview and is danger of falling out of their assessment window, RAs will conduct study assessments over the telephone. In addition to study questionnaires, at each study visit RAs will measure and record participants' height, weight, and blood pressure.

### 3.6.B. BLOOD

This study requires the collection of 22 mL of blood at baseline, 6-, 12-, and 18-month study visits. Blood will be tested for hemoglobin, platelets, CD4 count, HCV antibody and qualitative viral load (baseline and 18-months only), HIV viral load, high sensitivity C-reactive protein (HS CRP), total and HDL cholesterol (baseline and 18-months only), eGFR (creatinine), AST/ALT, and zinc levels (baseline and 18-months only). Zinc level testing will be performed in batches at ImmunoBioService laboratory. The remainder of the testing will be conducted at the Pasteur Laboratory.

Plasma samples will be stored for biomarker testing. Dried blood spot cards will be spotted using 60µL of blood per spot (or 300µL per card) and saved to be used for phosphatidylethanol (PEth) alcohol

biomarker testing. The incorporation of PEth will provide complement to self-report for alcohol consumption.

Blood will be collected prior to the assessment at baseline, 6-, 12-, and 18-month study visits. For a blood draw to be considered successful, one EDTA (8 mL) and one SST (3 mL) tube both must be at least  $\frac{3}{4}$  full. If the draw is successful, participants will be provided with full compensation and continue with the standard ZINC visit procedures. If the blood draw is unsuccessful at the participant's baseline visit, the participant will receive partial (1/3) compensation. The participant has 30 days after completion of the Screener to complete the blood draw. The participant will be disenrolled after three unsuccessful blood draw attempts or if more than 30 days have passed. The participant will be provided with full compensation at the third or final attempt. If the blood draw is unsuccessful at a follow-up study visit, the participant will be given partial (1/2) compensation for completion of the assessment. The participant will have 7 days to complete the second blood draw attempt. If this attempt is unsuccessful, the third attempt will be done at the next study visit (medication only visit). The participant will be provided with full compensation at the third attempt. For blood draw attempts that occur outside of the 7-day window, sections on medications and past 24-hour activities will be reassessed.

The following algorithm will be followed at the 18-month study visit for retesting HCV Ab/VL:

- If the participant is AB negative at baseline, they will be tested for Ab at 18-months, and if positive tested for VL. The rationale for this is that if the participant was found to be newly Ab positive at 18-months this would signal possible new HCV exposure requiring confirmation. If the VL is positive, this confirms new infection.
- If the participant is Ab positive and VL negative at baseline, they would only be tested for VL at 18-months. HCV Ab is not protective and therefore the individual remains at risk for re-infection if exposure, thus, necessitating re-testing VL at 18-months. While the additional nuance that there are a small number of patients who have a low fluctuating VL after initial infection, which may be intermittently negative before transitioning to chronic infection with high VL exists, this is beyond the scope of the study. For this study, we presumed that VL negative at baseline and VL positive at 18-months indicated new exposure and infection.
- Participants who are Ab and VL positive at baseline will not be re-tested at 18-months.

All participants will be offered pre-and post-counseling for HCV testing for new diagnoses.

Please see the study laboratory protocol for additional detailed information regarding phlebotomy and sample processing procedures.

### 3.6.C. URINE

A pregnancy test will be administered by trained clinical research staff at screening to determine eligibility and at each study visit.

Urine will also be used to measure adherence to the study medications via the added Riboflavin, as described in section on Adherence.

### 3.6.D. LIVER STATUS

As many of the biomarkers used to assess inflammation are synthesized in the liver, an inability to account for liver health makes interpretation of the biomarkers of inflammation (e.g., CRP) and their association with zinc and HIV disease progression, as well as, AMI and mortality risks difficult. Therefore to minimize confounding due to liver disease, two baseline measures of liver health (fibroscan and FIB-4 score) will be obtained. Fibroscan is a non-invasive ultrasonic imaging technique used as an alternative to liver biopsy. FIB-4 score is an inexpensive and accurate biomarker of liver fibrosis in HIV- and HCV-positive patients and those with alcohol disorders. The study team will calculate FIB-4 scores using baseline laboratory values for all study participants. Through consultation with a liver expert, the study team created an algorithm to place participants in one of three categories based on their FIB-4 values: high, low, and unclear possibility of liver cirrhosis. Participants that fall into the “unclear” category (FIB-4 values ranging from 1.4-3.25) will receive a fibroscan at their next study visit to determine their liver disease status. Fibroscans will be conducted at the First St. Petersburg Pavlov State Medical University at the participant’s 6-week assessment.

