### 2.7.A. SAMPLE SIZE CALCULATION AND POWER

Power was calculated for the overall primary study endpoint (change in VACS index score). Power calculations assumed a two-sided hypothesis test, with a significance level of 0.05. It was expected that 250 participants would be enrolled into the study. We anticipated 20% loss to follow-up due to death and participant withdrawal. Based on the VACS study, the standard deviation of the change in VACS index score from initiation of ART to after one year was 25. We expect the standard deviation will be similar in this study. Given these assumptions and with 200 evaluable participants (assuming 20% loss to follow-up, and 100 participants in each arm), the study is anticipated to have 80% power to detect a difference between the placebo and zinc groups in their mean changes in VACS index score over the 18-month period as small as 10 (e.g. 20 vs. 10 for the placebo and zinc groups, respectively) using a two-sided t-test.

Aim 2: To test the efficacy of zinc supplementation compared to placebo to slow HIV disease progression as measured by CD4 cell count. We anticipate analyzing log transformed values of change in CD4 cell count due to possible skewness in the data. Group differences will be back transformed from the natural log scale and therefore the parameter of interest is the ratio of the mean changes in CD4 cell count from baseline to 18 months for the zinc group relative to the placebo group, where change is defined as CD4 count at baseline - CD4 count at 18 months. The estimated coefficient of variation for the change in CD4 cell count from baseline to 18 months (baseline - 18 months) is 0.20 cells/ $\mu$ L. Given these assumptions, with 200 evaluable participants (100 in the zinc and placebo arms), the study will have 96.3% power to detect a ratio of 0.90 (zinc:placebo) between the mean changes of CD4 counts for the zinc and placebo groups using a two-sided t-test.

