The main analysis evaluating the impact of zinc on the primary study outcome (i.e., change in VACS index) will use multiple regression models that include randomization group (i.e., zinc vs. placebo) as the main independent variable. The regression analyses will control for the two block randomization stratification factors: heavy alcohol consumption during the past week and gender. In addition, the models will control for baseline characteristics that differ between groups in order to avoid confounding. Potential confounders of interest, measured at baseline, include demographics, past month alcohol use, age, gender, anti-inflammatory medication use, cardiovascular disease risk factors, HCV status, substance use (e.g., alcohol, smoking, cocaine), CD4 cell count, HIV-1 RNA, duration of awareness of HIV infection, and socioeconomic status. If the data are normally distributed, multiple linear regression models will be used. However, if the distribution is skewed, transformations of the data will be performed (e.g., log transformation). If an appropriate transformation is not identified, a median regression model will be used. The secondary outcomes, including HIV disease progression, as measured by change in CD4 cell count (Aim 2); the Reynolds risk score (Aim 3); and biomarkers of microbial translocation and inflammation (Aim 4) will be analyzed using the same approach described above. A secondary analysis will be conducted using a per protocol approach that includes only those participants who were adherent with their assigned intervention (i.e., taking zinc or placebo 80% of the time).

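### Baseline FIB-4 is calculated for everyone because liver health affects the inflammation markers, but no Aim 4 model prespecifies it; naming it as a fixed covariate is a free improvement whose gain in precision the documents cannot size.

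*Supplement*

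**What the plan says.** Protocol 3.6.D notes that many inflammation markers are made in the liver. It says that leaving liver health out of account makes the markers, and their relation to zinc, hard to read. Its response is: "Therefore to minimize confounding due to liver disease, two baseline measures of liver health (fibroscan and FIB-4 score) will be obtained". On coverage it says: "The study team will calculate FIB-4 scores using baseline laboratory values for all study participants". FIB-4 values are then sorted into three categories of cirrhosis likelihood. Only the unclear category (1.4 to 3.25) goes on to a fibroscan, at the 6-week visit.

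Protocol 8.1 and SAP 5.2 share the same modelling text. Besides randomized arm, the models always contain past-week heavy drinking and gender. Other baseline characteristics are added if the arms differ on them. The candidates are introduced as follows: "Potential confounders of interest, measured at baseline, include demographics, past month alcohol use, age, gender, anti-inflammatory medication use, cardiovascular disease risk factors, HCV status". The rest of that list covers substance use, CD4 count, HIV-1 RNA, time aware of HIV infection and socioeconomic status; no measure of liver fibrosis appears. Pairs of variables with a Spearman correlation above 0.4 are not entered together. The Aim 4 markers follow the same approach.

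SAP 4.5 names FIB-4 once, among the baseline descriptives tabulated by arm, and says that none of these will be tested. SAP 5.1 defines the main Aim 4 outcomes as 18-month levels of IL-6, D-dimer, sCD14, IFABP and LBP.

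**The concern.** The section that justifies collecting the liver measures and the section that specifies the models do not connect. Protocol 3.6.D presents liver status as something the analysis must take into account. The models leave its inclusion to chance imbalance, judged by a standard that is not stated: no threshold defines a difference, and SAP 4.5 rules out testing. The collinearity rule could then exclude FIB-4 alongside a correlated covariate, and the plan does not say which of a pair is kept.

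An imbalance rule is also the wrong gate for a prognostic variable. Adjusting for a baseline value that predicts the outcome reduces residual variance whether or not the arms differ on it. At stake are some efficiency in five secondary comparisons and some analyst discretion over a covariate that the protocol itself singles out.

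**Working it through.** **1. Reproduce the plan's own figures (protocol 2.7.A).** The inputs are: "Power calculations assumed a two-sided hypothesis test, with a significance level of 0.05"; "with 200 evaluable participants (assuming 20% loss to follow-up, and 100 participants in each arm"; "the standard deviation of the change in VACS index score from initiation of ART to after one year was 25"; and a detectable difference "in their mean changes in VACS index score over the 18-month period as small as 10".

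- Enrollment: 250 × (1 − 0.20) = 200 evaluable, as stated.
- VACS index: SE = 25 × √(2/100) = 3.536; 10/3.536 = 2.828; power = Φ(2.828 − 1.96) = 80.7% (80.4% with the noncentral t). The plan states 80%.
- CD4: the plan says "the study will have 96.3% power to detect a ratio of 0.90 (zinc:placebo" with a coefficient of variation of 0.20. The log-scale SD is √ln(1 + 0.20²) = 0.198 and the effect is |ln 0.90| = 0.105. Power is 96.4% (96.3% with the noncentral t).

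Both figures reproduce. Neither concerns Aim 4, for which the documents give no power, effect size or SD.

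**2. Trace the routes by which FIB-4 could enter an Aim 4 model.**

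- Fixed covariate: no.
- Named candidate confounder: no, although HCV status is named.
- Unnamed baseline characteristic on which the arms differ: possible. FIB-4 is tabulated by arm, and the candidate list is not worded as exhaustive. Entry then depends on chance imbalance and on surviving the r>0.4 rule.
- Interaction, ART, mediation and mortality analyses (SAP 5.4 and 5.5): not named.
- Imputation model (SAP 5.3): the current text does not list its variables, so use of FIB-4 there can be neither shown nor excluded.

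So no model prespecifies FIB-4, but one route remains open.

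**3. Illustrate what a fixed covariate could gain.** Let R² be the partial R-squared of baseline FIB-4 with a log marker at 18 months, given the other covariates. The documents do not give it, so the values below are assumptions. The starting point is a hypothetical comparison with 80% power, two-sided 0.05, and 200 evaluable participants.

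- SE ratio = √(1 − R²)
- Equivalent sample size = 200/(1 − R²)
- Power = Φ((1.96 + 0.842)/√(1 − R²) − 1.96)

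For R² = 0.10: 2.802/0.949 = 2.953; 2.953 − 1.96 = 0.993; Φ(0.993) = 84.0%.

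| Assumed partial R² | SE smaller by | Equivalent N | Power |
|---|---|---|---|
| 0 | 0% | 200 | 80.0% |
| 0.01 | 0.5% | 202 | 80.4% |
| 0.02 | 1.0% | 204 | 80.8% |
| 0.05 | 2.5% | 211 | 82.0% |
| 0.10 | 5.1% | 222 | 84.0% |
| 0.15 | 7.8% | 235 | 86.0% |

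The formulas apply to linear regression, on a log scale if needed. They do not carry over directly to the median regression that SAP 5.2 keeps as a fallback.

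**The case against.** The case on the other side has real force.

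- **Stated purpose.** Protocol 3.6.D collects the liver measures against confounding and never mentions precision. The rule in SAP 5.2 that admits imbalanced covariates has the same aim, so purpose and mechanism can be said to match. This stands: precision is an inference about what adjustment would deliver, not a goal the documents set for FIB-4.
- **Size.** The starting power and every R² value are assumptions, and at the low end the gain is negligible. This stands.
- **Link to the outcomes.** The only marker 3.6.D gives as an example is CRP, which is not among the five Aim 4 outcomes. The documents do not say which of the five depend on the liver. This stands, although 3.6.D speaks of many inflammation markers and not of CRP alone.
- **Overlap.** Past-week heavy drinking is always in the model, and HCV status and past-month drinking are named candidates. Each may carry some of the same information. The marker's own baseline value could be a more direct source of precision. SAP 5.1 lists change from baseline as a further secondary analysis, but the stated model for 18-month levels does not name the baseline marker. All this limits what FIB-4 could add; it does not show that it would add nothing.

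Two stronger readings are tempting. A reader might infer that FIB-4 is never used in any model. The documents do not support that, because the imbalance rule can admit it. A reader might also infer that the Aim 4 estimates are confounded by liver disease, or that a known amount of precision has been lost. Randomization handles the first in expectation for the zinc-placebo contrast, and the second would need an R² that the documents do not give.

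**Conclusion.** The point holds as a free improvement. The protocol gives a reason to account for liver health and obtains FIB-4 for everyone, yet no model commits to using it. The expected benefit is precision in five secondary comparisons. It ranges from negligible (standard error 0.5% to 1% smaller at a partial R-squared of 0.01 to 0.02) to a modest rise from 80% power to about 82%, 84% or 86% at 0.05, 0.10 or 0.15. These figures rest on an assumed R-squared net of the other covariates, an assumed 80% starting power, linear models and 200 evaluable participants. The primary outcome, the type I error rate and the absence of bias in expectation are unaffected. Not adjusting would be a legitimate choice, but the plan should make it openly.

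**What to change.** In SAP 5.2, name baseline FIB-4 as a fixed covariate in each Aim 4 model, on the log scale or in the three predefined categories (choose one in advance). Include it whether or not the arms differ on it, and exempt it from the r>0.4 screen. Because SAP 5.3 makes multiple imputation the primary intention-to-treat analysis, the imputation model should contain it too.

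Do not use the fibroscan as a covariate. Although 3.6.D calls it a baseline measure, it is done at 6 weeks, after randomization, and only in the unclear FIB-4 category.

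The cost is SAP wording, one or two degrees of freedom, and some overlap with HCV status and alcohol use. No new data are needed. The choice should be recorded before outcomes are examined by arm; after that, the adjusted model belongs among labelled sensitivity analyses.
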